ARFID is present in 1%–2% of the general population^5 6^ and was formally recognised in 2013.^7^ ARFID is a feeding and eating disorder characterised by an extremely restricted dietary quantity or variety resulting in significant weight loss, nutritional deficiencies, reliance on nutritional supplements and/or psychosocial impairment.^7^ In contrast to other EDs, ARFID occurs in approximately equal proportions of males and females,^6 8^ has an earlier age of onset^9^ and the restrictive eating is not primarily motivated by weight and shape concerns.^7^ ARFID is often accompanied by severe and sometimes life-threatening somatic and psychosocial comorbidities, leading to high social and financial burden for patients and their families.^10^,^14^ Despite the significant impairment, our knowledge on ARFID aetiology is limited. In part due to this insufficient understanding, evidence-based treatments are only starting to be developed^15^ and no specific treatment guidelines exist.^16^ A longer duration of untreated EDs other than ARFID has been found to decrease the likelihood of recovery.^17^ It is, therefore, likely that the lack of treatment options significantly contributes to the chronicity of ARFID.

ARFID is conceptualised as a single disorder; however, the Diagnostic and Statistical Manual of Mental Disorders fifth edition (DSM-5) describes three non-mutually exclusive presentations: (1) sensory-based food avoidance; (2) low appetite or interest in food and (3) fear of aversive consequences of eating. These symptom clusters overlap in a subset of individuals with ARFID (15%–51%).^818^,^20^ Comorbidities vary somewhat depending on the dominant presentation(s)^11 19^; for instance, sensory-based food avoidance has been shown to be more strongly related to neurodevelopmental conditions, low appetite or interest in food to mood disorders,^21^ and fear of aversive consequences to obsessive-compulsive disorder (OCD) and anxiety disorders.^11^

ARFID-related phenotypes such as appetite, food fussiness and food neophobia have been shown to be moderately to highly heritable.^22^,^25^ Our previous research using Swedish twin data further supports our aim of conducting a GWAS for ARFID: with a twin-based heritability of 70%–85%,^5^ ARFID is among the most heritable of EDs^26^ and of psychiatric conditions in general.^27^,^30^

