### Case definition

Cases will be participants who screen positive for ARFID on the PARDI-AR-Q or NIAS, report no clinically significant disordered eating behaviours in the last 28 days that could suggest the presence of AN or BN on PEDE-Q and have no lifetime diagnosis of AN or BN. Controls will be participants who screen negative for ARFID on PARDI-AR-Q and NIAS, report no clinically significant disordered eating in the last 28 days suggesting the presence of AN or BN on PEDE-Q, have no lifetime diagnosis of any ED or other psychiatric condition, and who have no first-degree relatives with an ED as reported by the parent. Case participants who will be included in the microbiome substudy will display exceptionally high scores on the PARDI-AR-Q subscale for sensory-based food avoidance (see table 1), and control participants will display exceptionally low scores on all PARDI-AR-Q and NIAS subscales. Table 1 presents detailed inclusion and exclusion criteria for cases and controls included in the main study and in the microbiome substudy.

**Table 1 T1:** Inclusion and exclusion criteria for the main study and the microbiome substudy

	Main study		Microbiome substudy	
	Cases	Controls	Cases	Controls
NIAS	PE>9 **OR** LA>8 **OR** F>9	PE≤9 **AND** LA≤8 **AND** F≤9		PE<5 **AND** LA≤1 **AND** F≤1
	**OR**	**AND**		**AND**
PARDI-AR-Q	A0 met **AND** (A1 **OR** A2 **OR** A3 **OR** A4) met	A0—A4 not met	S>5.5*	S≤1 **AND** LA≤1 **AND** F≤1
	**AND**	**AND**	**AND**	**AND**
EDE-Q	Global score <4 **AND** No vomiting **AND** No laxative use	Global score <4 **AND** No vomiting **AND** No laxative use **AND** <5 binge eating episodes		
	**AND**	**AND**		
Control questions	No lifetime diagnosis of AN or BN	No lifetime diagnosis of any ED **AND** No first degree relative with a lifetime diagnosis of any ED **AND** No current diagnosis of a psychiatric disorder	No antibiotics or probiotics during the last 3 months **AND** Never hormones for gender reassignment **AND** No current inflammatory GI condition	No antibiotics or probiotics during the last 3 months **AND** Never hormones for gender reassignment **AND** No current inflammatory GI condition

* Due to the dominance of sensory-based food avoidance in children with ARFID^69^ and in order to obtain a sufficient sample size for microbiome analyses, we focused our microbiome analysis on those with high scores on S to investigate the association of sensory-based food avoidance with the gut microbiome.

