#### Data analysis

Research data will be pseudonymised for data analyses. We will follow predetermined statistical analysis plans for phenotype, genotype and gut microbiome data. All analyses will include age and sex/gender as covariates and be corrected for multiple testing.

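### The microbiome contrast compares high-sensory ARFID, with or without low appetite or fear, with low-symptom children, so by itself it cannot show the sensory-specific association that the Table 1 footnote names

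*Protocol article*

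**What the plan says.** All the selection rules are in the protocol article under Case definition and in Table 1.

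- **Purpose.** The Table 1 footnote says "we focused our microbiome analysis on those with high scores on S to investigate the association of sensory-based food avoidance with the gut microbiome".
- **Substudy cases.** The text says "Case participants who will be included in the microbiome substudy will display exceptionally high scores on the PARDI-AR-Q subscale for sensory-based food avoidance". The table gives S>5.5 as the only symptom rule. The NIAS cell for substudy cases is empty, and nothing limits LA or F. The main-study NIAS route to case status is "PE>9 OR LA>8 OR F>9", so a case may score high on low appetite or fear.
- **Substudy controls.** The text says "control participants will display exceptionally low scores on all PARDI-AR-Q and NIAS subscales". The table requires "S≤1 AND LA≤1 AND F≤1" on PARDI-AR-Q and "PE<5 AND LA≤1 AND F≤1" on NIAS.
- **Overlap of presentations.** The Background says "These symptom clusters overlap in a subset of individuals with ARFID (15%–51" per cent.
- **Analysis.** Under Gut microbiome analysis, β-diversity is compared between cases and controls. Linear models relating phenotypic measures to microbial and dietary diversity are also planned, but the LA and F subscales are not named in them. Under Data analysis: "All analyses will include age and sex/gender as covariates and be corrected for multiple testing".

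**The concern.** The footnote names one dimension, sensory avoidance. The selection rules let the two groups differ on three: S is high in cases by design, LA and F are free in cases, and all three are held near the floor in controls (NIAS picky eating somewhat less tightly, at below 5). A lower diversity or an altered profile in cases could then reflect sensory avoidance, co-occurring low appetite or fear, or a mixture.

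The article itself treats the presentations as having different correlates. The Aim 1 hypotheses link sensory avoidance to autism, low appetite to depression and metabolic factors, and fear to anxiety and OCD. The Discussion says the microbial data may inform nutrition interventions, so it matters which presentation a finding is attached to.

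**Working it through.** The article states no numerical power or effect size for the substudy, so there is no figure to reproduce. The check has two parts.

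**1. What the contrast estimates**

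| Dimension | Cases | Controls |
|---|---|---|
| Sensory (PARDI-AR-Q S) | above 5.5 | at most 1 |
| Low appetite (PARDI-AR-Q and NIAS LA) | no limit | at most 1 on each |
| Fear (PARDI-AR-Q and NIAS F) | no limit | at most 1 on each |

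For a scalar outcome such as the Shannon index, in SD units, the expected case-control difference is

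Δ = bS + q × bO

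where bS is the effect of high sensory avoidance, q the share of cases who also have low appetite or fear, and bO the effect of that second presentation. The unadjusted contrast estimates Δ, not bS.

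**2. How large q × bO might be**

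Inputs: 100 cases and 100 controls (Aim 5); q = 0.15, 0.30 and 0.51 (the ends of the Background range and a value between); bO = 0.2, 0.5 and 0.8 (assumed). SE = √(2/100) = 0.141. The last column is the chance that a single unadjusted two-sided 5% test rejects when bS = 0: Φ(qbO/SE − 1.96) + Φ(−qbO/SE − 1.96).

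| bO | q × bO at q = 0.15 / 0.30 / 0.51 | Chance of rejection if bS = 0 |
|---|---|---|
| 0.2 | 0.03 / 0.06 / 0.10 | 5.5% / 7% / 11% |
| 0.5 | 0.075 / 0.15 / 0.255 | 8% / 19% / 44% |
| 0.8 | 0.12 / 0.24 / 0.41 | 14% / 40% / 82% |

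If sensory avoidance does have an effect, say bS = 0.5 with bO = 0.5, the share of the difference due to the other presentations is q × bO/(q × bO + 0.5): 0.075/0.575 = 13% to 0.255/0.755 = 34%.

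**3. Whether the selected sample can separate them**

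LA and F are uncapped in cases, so they can vary there. With q = 0.15 to 0.51, 85 to 49 of the 100 cases have neither. Treating the second presentation as present or absent, the adjusted group effect rests on those cases against the 100 controls:

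- SE = √(1/100 + 1/85) = 0.148, or √(1/100 + 1/49) = 0.174, against 0.141 unadjusted.
- Detectable d at 80% power = 2.80 × SE: 0.40 with all 100 cases, 0.41 with 85, 0.49 with 49.
- Power at d = 0.5: 94% with 100 cases, 92% with 85, 82% with 49.

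Separation is therefore feasible at a moderate loss of precision, but it needs an analysis that the article does not describe.

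**The case against.** The strongest reply is that the point rests on one clause of a footnote. The footnote mainly explains why high-S cases were chosen: that presentation dominates in children, and enough cases were needed. The Aim 5 hypotheses speak of ARFID as a whole, and for high-sensory ARFID against unaffected children the contrast is valid. This stands, and it limits the defect to the sensory-specific description.

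A second reply is that the separate microbiome analysis plan may adjust for LA and F. Age and sex/gender are named as covariates for all analyses, but not as the only ones, and the linear models of phenotypic measures could include the subscales. That is fair, and the absence of a covariate list is not held against the article. But the purpose and the selection rules are both fixed here, and they do not match as written.

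Three stronger readings are tempting and are not supported.

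- **That the data cannot separate the presentations at all.** They can, because LA and F may vary among cases. Nor can it be said that S is useless within cases: S>5.5 narrows its range, but the article does not give the PARDI-AR-Q maximum, so the remaining range cannot be judged.
- **That other presentations will be credited to sensory avoidance, with a false-positive rate of up to 82%.** The rejection figures rest on assumed effects, on a sensory effect of zero, and on an overlap range for ARFID in general rather than children with S>5.5. At 0.2 SD they stay at 5.5% to 11%. They also ignore the planned multiplicity correction, which would lower them for any one test.
- **That restricting cases to the main-study NIAS limits (LA≤8 and F≤9) would isolate the sensory presentation.** Controls are at or below 1 on both, so a gap remains.

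**Conclusion.** The point holds as a mismatch between a stated purpose and the selection rules. The contrast estimates the difference between high-sensory ARFID, with or without low appetite or fear, and low-symptom children. A sensory-specific association cannot be read from it alone.

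The size of the mixing is not known. It depends on the overlap among cases with S>5.5 and on the effects of low appetite and fear on the microbiome, and the article gives neither. The 0.03 to 0.41 SD range is an illustration that borrows the general 15%–51% overlap and assumes effects of 0.2 to 0.8 SD. This is a cheap improvement in what the substudy can conclude. It does not invalidate the substudy.

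**What to change.** 1. Reword the Table 1 footnote so that the main contrast is high-sensory ARFID, with or without low appetite or fear, versus low-symptom controls.
2. Rest any sensory-specific statement on a prespecified secondary analysis that uses the variation of LA and F among cases. Either adjust for LA and F as continuous scores, or compare cases with low LA and F against the same controls and report mixed-presentation cases as a separate stratum. Fix the definition of low LA and F before the microbiome data are seen.
3. State the remaining limit. Cases in the sensory-only stratum may still score above controls on LA and F, and continuous adjustment extrapolates from the case range to the control floor.

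Recruitment and data collection need not change: under Procedure, parents complete PARDI-AR-Q and NIAS at screening. The cost is precision. If the 15%–51% overlap applies, the sensory-only stratum keeps about 49 to 85 of 100 cases, and the detectable d at 80% power is about 0.41 to 0.49 instead of 0.40. A stricter definition of low LA and F would leave less residual mixing but fewer cases.

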### Biological samples

#### Saliva samples

Saliva sampling will be conducted using Oragene-DNA saliva self-collection kit (OG-500, DNA Genotek) by the participants at home and mailed back to KI Biobank. Parents will oversee the saliva collection. To guarantee safe transport and storage of the samples, the kits stabilise DNA at ambient temperature for several years.

#### Stool samples

Stool samples will be collected at home using the OMNIgene-GUT sample collection kit (OM-200, DNA Genotek) from participants included in the microbiome substudy. Parents will assist in conducting the stool collection and complete the Bristol Stool Scale.^50^ To guarantee safe transport and storage of the samples, the kits stabilise DNA at ambient temperature for 60 days. Prior to stool sampling, participants document their dietary intake in an online 24 hours food recall logbook.^51 52^

#### DNA extraction and genotyping

Saliva samples will be stored at KI Biobank. We will use standard DNA extraction protocols and GWAS genotyping via the Illumina global screening array chip, or optimal methods available at the time of genotyping. Cases and controls will be randomised to plates.

#### Microbial DNA extraction and metagenomic shotgun sequencing

Stool samples will be stored at KI Biobank. Microbial DNA extraction will be performed using a combination of physical disruption of the bacterial cells and chemical DNA purification. Whole genome shotgun sequencing will be performed using the Illumina NovaSeq platform to obtain high-resolution taxonomic and functional microbiome data. Raw sequence data will be quality filtered and trimmed to remove host DNA and bases with PHRED quality score <20, yielding analysis-ready data. As sequencing technology and bioinformatic tools continue to advance, we will use the most effective methods and tools available at the time of analysis.

### Additional data sources

Our data will be linked to nationwide Swedish health registers including the National Patient Register (NPR),^43^ the Prescribed Drug Register (PDR),^45^ the Medical Birth Register^44^ and the National Quality Register for Specialised Eating Disorder Treatment (Riksät/Stepwise).^46^ Register linkage is conducted by government agencies via the Swedish personal number. The NPR provides data on all inpatient care since 1987 and around 80% of specialised outpatient care since 2001,^43^ using International Classification of Diseases 10th revision classification since 1997. We will use the NPR to identify ARFID-related diagnoses; other EDs and psychiatric, neurodevelopmental and somatic conditions; as well as to track healthcare utilisation over time. Evidence shows strong agreement between ED diagnoses in the NPR and in Riksät/Stepwise, confirming the validity of NPR data for research.^53^ The PDR provides data on all drug prescriptions dispensed since 2005, with active drug ingredients categorised using the Anatomical Therapeutic Chemical (ATC) Classification System.^45^ We will use ATC codes to identify prescribed nutritional supplements and enteral nutrition relevant to ARFID and medication utilisation over time. Riksät/Stepwise contains data on ED treatment from around 100 specialised and general psychiatry units across 21 regions since 1999. We will extract diagnoses and clinical characteristics, such as symptom severity and impairment. Riksät offers broader coverage and includes DSM-IV subtypes, providing more extensive information than the NPR.^46^

For GWAS, we will combine our data with other completed, ongoing and planned collections conducted by PGC-ED. Refer to table 2 for the expected sample sizes at the time of analysis.

**Table 2 T2:** Sample sizes and availability of genotypes for the ARFID-GWAS meta-analysis

Study	Cases	Controls	Age	Available by
ASTRI	300	⁓18 000	6–12	Available
ARIES	1500	500	6–14	May 2025
ARFID-GEN	⁓3000	/	6–99	September 2024
EDGI2	⁓3000	⁓1300	15–99	March 2026
PGC-ED	1200	⁓42 000	15–99	Available

ARFID, avoidant/restrictive food intake disorder; ARFID-GEN, ARFID–Genes and Environment; ARIES, ARFID InitiativE Sweden; ASTRI, ARFID in the Swedish Twin Registry Initiative; EDGI2, Eating Disorders Genetics Initiative 2; GWAS, genome-wide association studies; PGC-ED, Eating Disorders Working Group of the Psychiatric Genomics Consortium.

### Planned data analysis

#### Data management

Data will be stored in accordance with KI rules for data protection. Identifying personal information will be stored with very high security and strict physical and computer access control. ARIES data will be part of the master database CEDIX (all data at CEDI). Participants are not identifiable other than by the research group. Prior to analysis, data are pseudonymised. The key connecting ID to participant identity is only available at the Department of Medical Epidemiology and Biostatistics at KI. To protect privacy, we will practise cell suppression and not report data on subgroups with fewer than five individuals.

#### Statistical power

For the phenotypic analyses, we would need 394 participants in both case and control group to detect a small effect size (0.2) at an alpha level of 0.5 and 80% power and are, therefore, well powered.

For GWAS analyses, we set α=5×10^−8^. GWAS meta-analysis will include >71 000 samples (9000 cases; 62 360 controls; table 2) and will have >80% power to detect common variants (minor allele frequency [MAF]>5%) with modest effect sizes (OR>1.25), and low frequency variants (MAF>1%) with moderate effect sizes (OR>1.59). We anticipate detecting medium to large genetic effects for ARFID, considering a twin-based heritability estimate of 79%^5^ and are, therefore, adequately powered. No published studies exist on the gut microbiota in ARFID to guide our power analyses. However, our given sample size of 100 cases and 100 controls exceeds sample sizes of most published studies on the gut microbiota in AN. We expect to be adequately powered to detect medium to large effect sizes.

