### Participants

#### Objective

We will recruit 1500 children and adolescents aged 6–14 years with ARFID and 500 age-matched controls from Sweden to be included in the main study. 100 children and adolescents aged 6–14 years with ARFID, and 100 age-matched controls will also be selected and included in the microbiome substudy.

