### Procedure

Parents/guardians of children and adolescents with ARFID who are interested in participation will be referred to the study website (www.ariesstudy.se) that provides detailed study information and contact details in case of questions (‘parents/guardians’ will henceforth be referred to as ‘parents’ for readability). To be eligible for participation, all individuals must have a valid Swedish personal number (a unique national identification number), which is required for both providing consent and linking to the Swedish National Health Registers. Study information is provided in three versions: for children (6–11 years), for adolescents (12–14 years), and for parents. If interested in participation, parents can register their child and provide online informed consent on the study’s website. Parents will complete online screening questionnaires covering ARFID and other disordered eating cognitions and behaviours including the Pica, ARFID and Rumination Disorder Interview-ARFID Questionnaire (PARDI-AR-Q),^47^ the Nine Item ARFID Screen (NIAS)^48^ and the parent version of the Eating Disorder Examination Questionnaire (PEDE-Q).^49^

The online screening questionnaires will be used to create a diagnostic algorithm for DSM-5 ARFID and determine eligibility and case status of the child. If the child is eligible for the study by parent-report, parents are instructed to complete additional questionnaires (some are mandatory, some are optional; online supplemental table S1). Additionally, we implemented optional self-report questionnaires for adolescents. A saliva sample collection kit including return packaging is mailed to the parent’s address with directions for saliva collection from the child. Those participating in the microbiome substudy will also receive a stool collection kit. Participation in the main study will be complete as soon as the kits are received by Karolinska Institutet (KI) Biobank and all mandatory questionnaires are completed. All participants receive two cinema tickets as soon as participation in the main study is complete. We do not provide participants in the microbiome substudy with additional reimbursement.

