### Assessment battery

Online supplemental table S1 presents our assessment battery including validated instruments measuring demographics; ARFID symptoms; other ED pathology; food intake; co-occurring psychiatric, neurodevelopmental, and somatic conditions and traits; treatment utilization; environmental exposures; impairment and quality of life; and parental stress and ED pathology. All mandatory assessments are parent-reported; additionally, we offer optional questionnaires to be completed by parents and adolescents. Completion of the entire assessment battery will take approximately 90 minutes and can be done across several sittings. Questionnaires are applied in Swedish and have been adapted for administration via Forsta (previously Confirmit).

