##### Phenotypic analyses

We will describe the ARFID sample to present demographics; ARFID symptoms, onset and course; other ED pathology; food intake; co-occurring psychiatric, neurodevelopmental and somatic conditions and traits; treatment utilisation; environmental exposures; impairment and quality of life; and parental stress and ED pathology. Depending on the distribution, we will compute mean/SD or median/IQR for continuous variables, and *N*/percent for categorical variables. To compare ARFID cases with controls on all outcomes, we will conduct generalised linear modelling.

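### The claim that the phenotypic analyses are well powered holds for outcomes measured on all participants, but probably not for the optional adolescent self-report outcomes it also covers

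*Protocol article*

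**What the plan says.** The Statistical power section of the protocol article gives one calculation for the phenotypic analyses: "we would need 394 participants in both case and control group to detect a small effect size (0.2"). The error rate is printed there as 0.5 and the power as 80%, and the section concludes from this that these analyses have enough power. The planned sample is in the Objective paragraph under Participants: "We will recruit 1500 children and adolescents aged 6–14 years with ARFID and 500 age-matched controls".

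Four other places determine which outcomes are measured on that whole sample.

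- Procedure: "Additionally, we implemented optional self-report questionnaires for adolescents". The same section gives the age bands of the study-information versions: "for children (6–11 years), for adolescents (12–14 years), and for parents". The article defines adolescents nowhere else.
- Assessment battery: "All mandatory assessments are parent-reported; additionally, we offer optional questionnaires to be completed by parents and adolescents".
- Aims: self-reported as well as parent-reported data are counted as part of the phenotypic repository.
- Phenotypic analyses: "To compare ARFID cases with controls on all outcomes, we will conduct generalised linear modelling".

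**The concern.** The conclusion follows only if the requirement is set against the full 1500 and 500. By the article's own description, self-report outcomes cannot be available on that sample: they come from part of the age range, and only from those who choose to answer. The power claim has no restriction, and the case-control comparison is announced for all outcomes, so the claim extends to comparisons with a much smaller denominator.

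What is at stake is the accuracy of a published design property. A reader who takes the section at its word will credit the adolescent self-report comparisons with 80% power for a standardised difference of 0.2, when the true figure may be well below that.

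**Working it through.** **Inputs from the article.** Standardised difference d = 0.2; power 80%; 394 per group; 1500 cases and 500 controls (3:1); age range 6–14; adolescents 12–14. Alpha is printed as 0.5 and sidedness is not stated.

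**Inputs assumed.** The share of participants aged 12–14 and the uptake of the optional forms. Neither is given, so both are shown as ranges. The same share and uptake are taken for cases and controls, which keeps the ratio at 3:1.

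**Step 1: reproduce the 394.** For equal groups, n = 2(z₁₋α/₂ + z₀.₈₀)²/d².

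- Two-sided alpha 0.05: 2 × (1.960 + 0.842)²/0.04 = 392.4, so 393. The t-based solution is 393.4, so 394. The stated figure is reproduced.
- One-sided alpha 0.05: 310.
- Alpha 0.5 as printed: 115 two-sided (107 t-based), 36 one-sided.

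Only two-sided 0.05 gives 394, and it is used below.

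**Step 2: power on the full sample.** Power ≈ Φ(d/SE − 1.960), with SE = √(1/n_cases + 1/n_controls) in SD units. For 1500 and 500, SE = 0.0516 and d/SE = 3.87, which gives **97%**. This is before the planned multiplicity correction.

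**Step 3: requirement at 3:1.** n_controls = (1 + 1/3)(1.960 + 0.842)²/0.04 = 261.6, so 262. The t-based solution is 262.1, so **263 controls and 789 cases**. As a share of the planned sample, 263/500 = 52.6%. The benchmark for a 3:1 subset is therefore 263 controls, not 394.

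**Step 4: the adolescent subset.** With ages spread evenly, 3 of the 9 years of age fall in 12–14, so there are 1500 × 3/9 = 500 cases and 500 × 3/9 ≈ 167 controls. The effect detectable with 80% power is 2.802 × SE.

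| Uptake | Cases / controls | SE | Power for d = 0.2 | Detectable d at 80% |
|---|---|---|---|---|
| 100% | 500 / 167 | 0.0894 | 61% | 0.25 |
| 80% | 400 / 133 | 0.1001 | 51% | 0.28 |
| 50% | 250 / 83 | 0.1267 | 35% | about 0.36 |

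**Step 5: other age distributions.**

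| Share aged 12–14 | Controls, full uptake | Power, full uptake | Power, 75% uptake |
|---|---|---|---|
| 20% | 100 | 41% | 32% |
| 33% | 167 | 61% | 49% |
| 40% | 200 | 69% | 56% |
| 50% | 250 | 78% | 66% |
| 60% | 300 | 85% | 74% |

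The 80% target is reached only when the share aged 12–14 multiplied by the uptake is at least about 53%.

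**Step 6: optional parent questionnaires.** These are open to parents of children of all ages, so only uptake matters. By Step 3 they fall below 80% power if uptake is under about 53%.

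**The case against.** The strongest reply is that nothing has been miscalculated. The 394 is correct, 1500 and 500 exceed it, and the conclusion is right for every mandatory outcome. A separate power figure for optional add-on instruments is something a condensed article may leave to the analysis plans it refers to. This stands in part: the absence of such a figure would not be a finding on its own. The point is that the article states a conclusion, without limit, that its own data-collection scheme does not support for some of the outcomes covered.

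Second, Aim 1 says that most, not all, of the variables will be compared between cases and controls, and the Phenotypic analyses section lists domains rather than instruments or informants. The self-report scales may therefore not all be tested. This weakens the point without removing it, because the analysis section itself speaks of all outcomes.

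Third, the 12–14 band is attached to the study-information versions, and the supplementary assessment table is not at hand. That the band also governs self-report is the natural reading, but it is an inference. The age distribution and the uptake are assumptions as well.

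Some stronger readings are not supported.

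- A reader might set 167 controls against 394 and infer a shortfall of more than half. The 394 is the 1:1 requirement; at 3:1 the comparison is 167 against 263.
- A reader might infer that the phenotypic analyses as a whole are underpowered. At 97% for full-sample outcomes, they are not.
- A reader might infer that the optional parent questionnaires fall short. Nothing in the article indicates uptake below 53%.
- A reader might infer that null self-report results will be taken as evidence of no effect. No passage says so, and none of the Aim 1 hypotheses names self-report.

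**Conclusion.** The statement holds for outcomes collected on all 1500 cases and 500 controls. It probably does not hold for adolescent self-report. If one third of participants are 12–14, power for d = 0.2 is at most 61%, falling to 35% at 50% uptake, against the stated 80%. The detectable effect rises from 0.2 to about 0.25 and 0.36 respectively.

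This rests on two-sided alpha 0.05, an even age spread, adolescents meaning 12–14, and an unchanged 3:1 ratio. It does not depend closely on the even spread: at least about 53% of participants would have to be 12–14, and every one of them would have to answer, before the claim became true. Correction for multiple testing, which the article plans, would lower all of these powers.

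The consequence is limited, because the forms are optional and supplementary. The printed alpha of 0.5 in the same sentence is a separate and certain error: it is incompatible with the 394.

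**What to change.** In the Statistical power section:

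1. Restrict the well-powered statement to outcomes collected on all participants.
2. For adolescent self-report and other optional outcomes, give the expected numbers with data and the effect detectable with 80% power. On the assumptions above, this would be about 0.25 at 500 cases and 167 controls, and about 0.36 at 250 and 83. The observed age distribution and completion rates should replace these assumptions once known.
3. Replace the printed alpha of 0.5 with two-sided 0.05, the value that gives 394.

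Labelling the optional comparisons exploratory is a matter of choice and is not needed to correct the claim. The cost is about two sentences and one corrected number. No additional participants or data are required; the only loss is a less favourable figure for the optional outcomes.
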